#### Participant Compliance

##### Informed Consent

A thorough process must be followed to secure participant understanding and cooperation. The investigational product and required laboratory tests must be provided free of charge.

##### Compliance Monitoring

The medication measurement should be used to monitor adherence. Compliance should be calculated as follows: (actual medication dose administered / planned medication dose) × 100%. Compliance between 80% and 120% is deemed acceptable.

##### Management of Poor Compliance

All concomitant medications in the eCRF should be recorded. Follow-up for participants with poor therapeutic response or compliance must be intensified (<80% or >120%).

### Evaluation

#### Primary Outcome

Difference in TPOAb levels before and after treatment.

#### Secondary Outcomes

TGAb, TSH, T3, T4, FT3, FT4, thyroid ultrasound,IL17 mRNA,FOXP3 mRNA (peripheral blood),TCM syndrome score, quality of life scale score.

#### Security Outcome

Blood routine, urine routine, hepatic and renal function, and electrocardiogram.

#### Adverse Event Observation and Recording

Following entry into the clinical trial, the patient’s vital signs, symptoms, any adverse events related to the disease, and laboratory parameters will be recorded. Thus, the occurrence of adverse events may not necessarily be related to the study drugs. Adverse events were assessed and graded according to the Common Terminology Criteria for Adverse Events (CTCAE) version 5.0. Grade 1 (mild): asymptomatic or mild symptoms; clinical or diagnostic observations only; intervention not indicated. Grade 2 (moderate): minimal, local, or noninvasive intervention indicated; limiting age-appropriate instrumental activities of daily living. Grade 3 (severe or medically significant): medically significant but not immediately life-threatening; hospitalization or prolongation of hospitalization indicated; disabling; limiting self-care activities of daily living. Grade 4 (life-threatening): urgent intervention indicated. Grade 5 (death): death related to the adverse event. The initial report of any serious adverse event must be made within 24 hours of discovery to the principal investigator, [name]. The principal investigator is responsible for ensuring the subsequent report is escalated to the Research Administration Office at Yueyang Hospital of Integrated Traditional Chinese and Western Medicine ([contact], extension Research Admin). The final mandatory report must be submitted to the Drug Research Supervision Department of the National Medical Products Administration ([contact]). Any causal relationship between the adverse event and the investigational drug will be determined by classification. All serious adverse events were followed until resolution or until the event was considered stable.

In the case of a serious adverse event in a participant, the details of the medication must be disclosed, and unblinding can only be performed with the consent of the principal investigator. Once an emergency letter has been read, the case will be considered a dropout.

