### Blinding

Blinding preservation: a two-tier blinding approach was implemented, with the first tier involving the assignment of group codes corresponding to each drug number (Group A or Group B), and the second tier involving the concealment of the actual drug types for the two groups. Sealed blinding documentation was duplicated and entrusted to the clinical research unit for safekeeping.

Blinding procedures: this study used a double-blinded method. Both blinding processes were overseen by the designated personnel responsible for maintaining the blinding. The first blinding involved the specification of Groups A and B, whereas the second blinding involved specifying the test and control groups. Blinding procedures were overseen by the project leader of the clinical study unit, the principal investigator, and the statistician. Randomization order not available to participant registrars and intervention assigners

Emergency blinding: emergency blinding was permitted in the event of serious complications or adverse events during the study that could impact conduct and treatment decisions. In such cases, the researcher, project leader, and clinical supervisor were required to be present, and detailed records of the reason, time, and location of blinding were documented and signed. All data were preserved.

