#### Dropout Analysis

The chi-square test was used to compare the overall dropout rate between the 2 groups. Differences in demographic characteristics, treatment received, and other variables of the dropout participants from the experimental and control groups were described and analyzed to understand the reasons for dropout.

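### The two emergency unblinding rules have different triggers, and reading the emergency letter makes a participant a dropout although the withdrawal criteria do not say so

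*Protocol article*

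**What the plan says.** Two sections of the protocol article govern opening the code.

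- **Blinding** (the text prints blinding where unblinding is evidently meant): "emergency blinding was permitted in the event of serious complications or adverse events during the study that could impact conduct and treatment decisions". On procedure, "the researcher, project leader, and clinical supervisor were required to be present", and the reason, time and place are recorded and signed. The paragraph ends by saying that the data were preserved.
- **Adverse Event Observation and Recording**: after a serious adverse event, the rule is that "the details of the medication must be disclosed, and unblinding can only be performed with the consent of the principal investigator". The consequence follows: "Once an emergency letter has been read, the case will be considered a dropout".

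Neither section refers to the other. The Blinding section names "the project leader of the clinical study unit, the principal investigator, and the statistician" as overseers of the blinding procedures, so it treats the project leader and the principal investigator as separate roles.

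The criteria for strike-out, discontinuance and shedding say when a participant leaves. Discontinuation criterion 2.1 covers an adverse or serious adverse event only where it makes the participant unsuitable to continue. The desertion criteria are poor compliance, incomplete records that affect the efficacy evaluation, and the participant's own withdrawal. Code-breaking is not among them.

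**The concern.** There are two linked problems.

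First, one rule is a conditional permission and the other is an obligation for serious adverse events. The obligation is itself subject to consent in the same sentence. A reader cannot tell from the article which serious adverse events should lead to an opened code.

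Second, opening the code carries a consequence for the data: the participant becomes a dropout. Dropout status is used in the analysis, where "The chi-square test was used to compare the overall dropout rate between the 2 groups". If the label also means that week-12 TPOAb is not taken, or is set aside, the participant enters the primary analysis as missing. The loss then follows from a safety event after randomisation. Such events may be commoner in one arm, and those who have them may differ in antibody change from those who do not. That is a route to bias in the between-arm comparison, created by a rule and not by the participant's own departure.

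**Working it through.** The first part is a comparison of text.

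**Trigger, case by case**

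1. A serious adverse event that could affect conduct or treatment decisions: permitted under Blinding, and to be disclosed with consent under Adverse Event Observation and Recording. A site can comply with both.
2. A serious adverse event that could not affect such decisions: outside the permission in Blinding, yet inside the obligation in the other section. Here the rules conflict.
3. A non-serious adverse event that could affect decisions: arguably covered by Blinding, depending on whether serious qualifies only complications or also adverse events. The other section is silent.
4. A serious adverse event for which the principal investigator withholds consent: the two halves of the sentence in Adverse Event Observation and Recording cannot both be met.

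**Authorisation**

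Blinding asks for three roles to be present. The other section asks for the consent of a further role. A site can obtain the consent and then open the code with the three present. The lists differ without excluding each other.

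**Dropout status**

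Under criterion 2.1 a participant with a serious adverse event who is still suitable stays in. Under the emergency-letter rule the same participant is a dropout once the letter is read. The emergency-letter rule is therefore wider than the withdrawal criteria.

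**Scale**

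Inputs from Sample Size Calculation: mean changes 120 and 20 (difference δ = 100), SD σ = 200 in each arm, two-sided α = 0.05, power 80%, 64 calculated, 70 per arm after dropout.

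- Normal approximation: n = 2(1.960 + 0.842)² × 200² / 100² = 62.8, so 63 per arm. The two-sample t-test gives 63.77, so 64, which reproduces the stated figure.
- Margin: 70 − 64 = 6 per arm, 12 in all.
- Power = Φ(δ / (σ√(2/n)) − 1.960). At n = 70: Φ(2.958 − 1.960) = 84.1%. At 64: Φ(2.828 − 1.960) = 80.7%. At 62: Φ(2.784 − 1.960) = 79.5%.

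A few extra losses therefore cost little power. Bias is the issue. As an illustration only, suppose k of 70 in one arm are unblinded and left out, their mean change differs from the rest of that arm by d, and the other arm loses nobody. The complete-case arm mean then moves by (k/70) × d. With d assumed to be one SD (200):

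- k = 1: 200/70 = 2.9
- k = 6, the whole margin in one arm: 6 × 200/70 = 17.1

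The planned difference is 100. Both k and d are assumptions. The documents give no serious adverse event rate, so the real k cannot be computed.

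**The case against.** The strongest defence has four parts.

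- **The rules can be combined.** Consent first, then opening with three roles present, satisfies both sections. This stands for authorisation. A reader might infer from the different names that the gatekeepers contradict each other; the text does not support that. It does not rescue the trigger, because a permission limited to certain events does not cover an obligation for all serious ones.
- **Disclosure is not truly mandatory.** It is gated by consent, and the English is loose; the sentence might mean only that consent is needed whenever disclosure is required. That reading is possible and would bring the two sections close together. It also shows that the sentence needs rewriting. A reader might infer that every serious adverse event will be unblinded and lost; the consent clause does not support so firm a reading.
- **Sites will not diverge.** Serious adverse events go to one principal investigator within 24 hours, and staff are trained. This stands: nothing in the article shows that the three sites would follow different sections, or that access to treatment information would be delayed. It is also tempting to set an assumed 1% to 5% of 140 (1.4 to 7 participants) against none under the permissive rule. The documents do not support that contrast: no rate is given, many of the same events could be unblinded under either rule, and some of these participants would leave under criterion 2.1 anyway.
- **The analysis copes.** The data are preserved, and the plan has multiple imputation, a complete-case comparison, a missing-not-at-random analysis and a worst-case analysis. This stands in part. The dropout label does not say that week-12 TPOAb is discarded. Nor does any passage say that it is kept, and if an observed value is treated as missing, imputation or a worst-case score replaces data that exist.

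A condensed article may leave out the detail of code-breaking. Here, however, two rules and an automatic consequence are stated, and they need to agree.

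**Conclusion.** The point holds on two counts: the triggers do not match, with an internal tension in the adverse event section; and the automatic dropout rule goes beyond the article's own withdrawal criteria. The second matters more to the analysis, because it can tie missing primary data to a safety event after randomisation that may differ by arm. That step assumes that dropout status leads to week-12 TPOAb being uncollected or unused, which the article neither states nor rules out.

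The number affected is unknown and, if serious adverse events are few, probably small against 6 per arm. No effect on the primary result is shown. The change is still worth making, because it costs almost nothing and closes an avoidable route to bias.

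**What to change.** 1. Reconcile Blinding with Adverse Event Observation and Recording into one trigger and one authorisation procedure for all three sites. The clinical team decides the content of both.
2. Replace the automatic dropout sentence with a statement that code-breaking alone does not remove a participant from follow-up or analysis. Week-12 TPOAb is still collected where possible, and any available value is analysed in the assigned arm. Whether treatment continues remains a separate clinical decision.
3. List opened codes by arm, with the reason and whether week-12 TPOAb was obtained.

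The article schedules the end of data collection in 2025 (May in Results, October in the Abstract), so item 1 may now serve mainly to document which rule was followed. Items 2 and 3 can still be applied to the data in hand. The Abstract says that analysis has not been performed and Results says that it is in progress, so the decision should be dated and recorded before treatment groups are revealed, if that is still possible.

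The cost is a change of wording, a note to sites and one listing, with no new staff. The downside is that a few unblinded participants stay in the analysis. For a laboratory value such as TPOAb that is a small price; for the self-reported scales, a check without them could be shown alongside.

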#### Evaluation Index Detection Method

Serological analysis was conducted at the laboratory department of Yueyang Hospital of Integrated Traditional Chinese and Western Medicine, affiliated with Shanghai University of Traditional Chinese Medicine. Blood-related parameters were assessed using a Roche automatic electrochemiluminescence immunoassay analyzer (Roche Diagnostics GmbH) and its corresponding kits. Patients refrained from eating after 8 PM the evening before blood collection and fasted from 8 PM to 9 AM on the day of collection. Subcenter serum samples were transported from a 4 ℃ incubator to the main laboratory department within a 2-hour timeframe.

Thyroid ultrasound assessment: thyroid color Doppler ultrasound evaluations were conducted in the B ultrasound facility at each research center. Measurements of the width, thickness, and isthmus thickness of the left and right thyroid lobes were taken and documented.

*IL17* and *FOXP3* mRNA levels were assessed in venous blood samples collected from all patients before and after treatment. Specifically, 5 mL of venous blood was drawn into EDTA tubes, from which 250 μL was aliquoted into 1.5 mL EP tubes. Subsequently, 750 μL of Trizol was added to each tube, and the samples were stored at –80 ℃ for subsequent analysis. The quantification of *IL17* and *FOXP3* mRNA levels in peripheral blood was conducted using fluorescence quantitative PCR.

The TCM symptom score scale (see Multimedia Appendix 4 for the Symptom Score Scale) was revised for HT of liver depression and spleen deficiency type based on clinical syndrome characteristics. This revision, guided by the Beijing expert consensus on HT treatment (2021) [18], involved input from three highly experienced TCM internal medicine clinicians and preliminary investigation findings. The scale encompassed 7 items: main symptoms (fatigue, depression, irritability), secondary symptoms (abdominal distension, pain, excessive breathing, insomnia), and tongue and pulse characteristics (white or greasy fur, stringy or deep pulse). Patients were assessed for symptom severity and assigned scores, with higher scores indicating greater improvement in TCM syndromes.

The Thyroid-Specific Patient-Reported Outcome questionnaire-39-item (ThyPRO-39) scale (see Multimedia Appendix 5 for the Quality of Life Scale) is a reliable and valid instrument designed to assess the quality of life in patients with benign thyroid conditions [19]. It comprises 39 items categorized into 13 subscales, covering somatic symptoms (goiter, hyperthyroidism, hypothyroidism, and eye symptoms), physiological and psychosocial symptoms (fatigue, cognition, anxiety, depression, emotional susceptibility, social activities, daily life, and appearance), and overall quality of life. Each item is scored on a 5-point Likert scale. Subscale scores are calculated by averaging the item scores, dividing by 4, and multiplying by 100, resulting in a standard score ranging from 0 to 100. Higher scores on the ThyPRO-39 indicate a lower quality of life [20].

### Statistical Analysis Method

#### Statistical Software

For statistical analysis of data in this study, SAS 9.2 (SAS Institute) statistical software was used.

#### Fundamental Principles

In this study, all statistical inferences were made using a 2-sided test at a significance level of α=.05. The confidence intervals of the study parameters were estimated using 2-sided 95% CIs to indicate the statistical significance of differences.

#### Handling Missing Data and Sensitivity Analysis Plan for Missing Data

Missing data will be handled using Multiple Imputation under the assumption of Missing at Random. Multiple (eg, m=20) complete datasets will be generated by imputing missing values using a multivariate model incorporating key baseline and outcome variables. The planned primary and secondary analyses will be performed separately on each imputed dataset. Final estimates (eg, treatment effects, confidence intervals, and *P* values) will be obtained by pooling the results from all m datasets using Rubin rules. A sensitivity analysis assuming a Missing Not at Random scenario will be conducted to assess the robustness of the conclusions. Safety evaluations were not performed for missing data.

To ensure the robustness of the conclusions from the primary analysis, the following prespecified sensitivity analyses will be performed regarding missing data. First, the results from the primary analysis using multiple imputation will be compared with the results from an analysis based on the complete-case dataset. Second, a worst-case scenario analysis will be conducted. This analysis will assume that all participants in the intervention group with missing primary outcome data experienced treatment failure (eg, no symptomatic improvement or no reduction in antibodies), while all participants with missing data in the control group experienced treatment success. The primary outcome will be re-evaluated under this extreme assumption. These sensitivity analyses aim to assess whether the study conclusions are sensitive to the methods used for handling missing data. Consistency between the results of these analyses and the primary analysis would provide stronger support for the reliability of the final conclusions.

#### Dropout Analysis

The chi-square test was used to compare the overall dropout rate between the 2 groups. Differences in demographic characteristics, treatment received, and other variables of the dropout participants from the experimental and control groups were described and analyzed to understand the reasons for dropout.

#### Statistical Description

In this study, quantitative variables were summarized using their mean, SD, minimum, maximum, Q1, median, and Q3. Confidence intervals were provided when necessary. Quantitative variables were expressed as “mean and SD” if they followed a normal distribution and “median and IQR” if they did not follow a normal distribution. Qualitative variables are summarized in terms of frequency distribution and composition ratio.

#### Inferential Statistics

Baseline data, efficacy indicators, and safety indicators underwent inferential statistical analysis. Baseline data: statistical inferential analysis was conducted based on the type of variable to compare the comparability of the participants in the experimental and control groups. Quantitative variables were analyzed using 2-tailed *t* tests for normally distributed data and nonparametric rank-sum tests for nonnormal distribution. Qualitative variables were analyzed using chi-square tests. Efficacy indicators: comparative analysis of quantitative variables within groups was conducted using paired *t* tests for normally distributed data and paired nonparametric rank-sum tests for nonnormal distribution. Differences in efficacy indicators before and after the intervention were calculated separately for the experimental and control groups, and *t* tests or rank-sum tests were used to assess the statistical significance of these differences. Analysis of covariance, which considers the center effect, was used to provide the mean (or adjusted mean), difference in means, and 95% CIs for each group. Paired chi-square tests were used for qualitative variables, and the Wilcoxon rank-sum test was used for ranked variables. If the baseline comparability of the experimental and control groups was poor, general linear models and logistic regression models were applied for adjustment. Safety analysis: the chi-square test was used to compare the incidence of adverse events between the 2 groups, and a list was used to describe the adverse events that occurred in the trial. Intergroup and intragroup comparisons of quantitative indicators were performed using the corresponding differential tests. Laboratory test results were analyzed for changes in normal/abnormal values before and after the study, and a list was provided for abnormal values.

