## Methods

### Study Design

This is a randomized, double-blind, placebo-controlled, multicenter clinical trial in which the participants are randomized in a 1:1 ratio to either the treatment group (KDGs group) or the control group (placebo group). Each group will undergo a 12-week treatment. See Multimedia Appendix 1 for the SPIRIT (Standard Protocol Items: Recommendations for Interventional Trials) 2025 checklist [15].

We will record all baseline observations during the screening period. Throughout the treatment period, participants will have monthly follow-up visits and complete TCM evidence-based efficacy and quality of life scale score assessments. TPOAb, TGAb, thyroid stimulating hormone (TSH), triiodothyronine (T3), thyroid hormone (T4), serum free triiodothyronine (FT3), serum free thyroxine (FT4), thyroid ultrasonography, and *IL17* mRNA and FOXP3 mRNA levels will be examined and recorded before and after treatment. The schedule of participants is shown in Table 1.

**Table 1 table1:** Study schedule of assessments.

Item	Baseline (day 7~0)	0 weeks (day 0; visit 1)	4 weeks (day 28; visit 2)	8 weeks (day 56; visit 3)	12 weeks (day 84; visit 4)
Informed consent	✓				
Inclusion/exclusion criteria	✓				
Demographic information	✓				
History taking and recording	✓	✓	✓	✓	✓
Physical examination	✓	✓	✓	✓	✓
Traditional Chinese medicine evidence-based efficacy score		✓	✓	✓	✓
Quality of life scale score		✓	✓	✓	✓
Electrocardiogram	✓				✓
Blood test	✓				✓
Urinalysis	✓				✓
Liver function	✓				✓
Kidney function	✓				✓
TPOAb^a^	✓				✓
TGAb^b^	✓				✓
TSH^c^	✓				✓
T3^d^	✓				✓
T4^e^	✓				✓
FT3^f^	✓				✓
FT4^g^	✓				✓
IL^h^-17/FOXP3	✓				✓×
Thyroid ultrasound	✓				✓
Record of study drug usage	✓	✓	✓	✓	✓
Adverse event record	When necessary	When necessary	When necessary	When necessary	When necessary
Record of combined medication use	✓	✓	✓	✓	✓
Analysis of causes of shedding	✓	✓	✓	✓	✓

^a^TPOAb: thyroid peroxidase antibody.

^b^TGAb: thyroglobulin antibodies.

^c^TSH: thyroid stimulating hormone.

^d^T3: triiodothyronine.

^e^T4: thyroid hormone.

^f^FT3: free triiodothyronine.

^g^FT4: free thyroxine.

^h^IL: interleukin.

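### The efficacy analyses mix within-arm tests with between-arm ones: the default test for qualitative outcomes cannot compare the arms, paired tests are not ranked below the comparison, and the week 4 and 8 scores have no stated role

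*Protocol article*

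**What the plan says.** All of the following is in the protocol article.

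- **Within-arm tests.** Under efficacy, Inferential Statistics begins with "comparative analysis of quantitative variables within groups was conducted using paired" t tests, or paired rank-sum tests if the data are not normal.
- **Change scores.** It continues: "Differences in efficacy indicators before and after the intervention were calculated separately for the experimental and control groups", and t or "rank-sum tests were used to assess the statistical significance of these differences".
- **ANCOVA.** The next sentence reads: "Analysis of covariance, which considers the center effect, was used to provide the mean (or adjusted mean), difference in means, and 95% CIs".
- **Qualitative and ranked variables.** "Paired chi-square tests were used for qualitative variables, and the Wilcoxon rank-sum test was used for ranked variables".
- **Further adjustment.** General linear and logistic models come in only if the arms turn out poorly comparable at baseline.
- **Data collected.** Study Design states that "participants will have monthly follow-up visits and complete TCM evidence-based efficacy and quality of life scale score assessments", and Table 1 ticks both scores at weeks 0, 4, 8 and 12. Secondary Outcomes lists "TCM syndrome score, quality of life scale score" with no time point.

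**The concern.** Three things are at issue.

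1. A paired chi-square looks at change in the same patients. It says nothing about whether one independent arm did better than the other. It is nevertheless the only default test named for qualitative efficacy variables.
2. Change within an arm mixes drug effect, natural course and placebo response, and the placebo arm exists to separate these. Listing paired tests among the efficacy analyses, with no statement that only the between-arm contrast counts, leaves room to report a significant change on KDGs beside a non-significant one on placebo as if it were evidence of effect. The paired tests cover every quantitative efficacy indicator, so this reaches TPOAb as well as the secondary outcomes.
3. The two patient-facing scales are measured at three post-baseline visits. The stated analyses are framed as before against after, with no visit term and no named use for weeks 4 and 8. The Conclusions say the trial will give evidence on TCM syndromes and quality of life, so how these scales are analysed matters.

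**Working it through.** **Is the paired chi-square a slip of wording?** The same section uses an ordinary chi-square to compare the arms at baseline and on adverse events, and Dropout Analysis does so for dropout rates. The word paired appears only for efficacy, so it reads as deliberate. Logistic regression, the one between-arm method that would suit a binary outcome, is conditional on poor baseline comparability. By default, then, no between-arm test of an unordered qualitative efficacy variable is named.

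**Within-arm tests when there is no treatment effect.** Inputs from Sample Size Calculation: SD of TPOAb change 200 in each arm, control-arm change 20, difference 100, two-sided α 0.05, power 80%, 64 per arm. These inputs reproduce the plan's own figure: 2 × (1.960 + 0.842)² × 200² / 100² = 62.8, so 63 by the normal approximation; the t-based calculation gives 63.8, so 64.

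Now let both arms have the same true change μ. The paired test in one arm has non-centrality μ/200 × √64 = 0.04μ. Let p be its power from the non-central t with 63 degrees of freedom. The arms are independent, so the chance that KDGs is significant and placebo is not is p(1 − p).

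| Common change μ | p | p(1 − p) |
|---|---|---|
| 20 | 0.124 | 10.8% |
| 40 | 0.351 | 22.8% |
| 50 | 0.504 | 25.0% |
| 60 | 0.657 | 22.5% |
| 100 | 0.976 | 2.3% |

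A two-sided 5% between-arm test would favour KDGs wrongly in 2.5% of trials. The value p(1 − p) peaks at p = 0.5, so 25% is a ceiling. At the plan's own control-arm change of 20 the figure is 10.8%, about four times 2.5%.

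**Baseline adjustment of the two scales.** Take equal variance σ² at week 0 and week 12 and correlation r between them; the article gives no r. Per-patient variance is 2σ²(1 − r) for a change score and σ²(1 − r²) for ANCOVA on the week-0 score. The ratio is (1 + r)/2:

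- r = 0.3: 0.65
- r = 0.5: 0.75
- r = 0.7: 0.85

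This gain arises only if the planned ANCOVA does not already include the week-0 score.

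**What weeks 4 and 8 add.** In a repeated-measures model with unstructured covariance and complete data, the week-12 contrast is essentially the week-12 ANCOVA. The earlier visits help mainly for participants who lack week 12. At the planned 10% dropout that is about 7 of 70 per arm.

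**The case against.** The strongest reply is that the plan does compare the arms. A reader might infer from the before/after wording that the scales are never compared between arms, or are analysed only as raw change. The documents do not support that: the t or rank-sum test on change is most naturally a between-arm test, although this is not said outright, and the ANCOVA with centre yields a difference in means with a 95% CI. This part of the objection stands in full.

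A reader might also infer that the week-0 score is left out of the ANCOVA. The article names centre and mentions adjusted means but gives no covariate list, and a condensed article may leave that list to the analysis plan. What can be said is that baseline is not stated to be a covariate, and that reserving further model adjustment for poor comparability leaves its inclusion in doubt.

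Nor is it shown that weeks 4 and 8 go wholly unused. The multivariate imputation model in Handling Missing Data might take them in.

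The article also nowhere commits to claiming superiority from within-arm results, and no listed outcome is expressly qualitative: they are laboratory values, mRNA levels, scale scores and ultrasound dimensions. This limits the reach of the chi-square error without removing it. A test for qualitative efficacy variables is stated, and it is the wrong kind. The worst-case sensitivity analysis also speaks of treatment success and failure, so a binary outcome may be needed.

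**Conclusion.** The point holds in a limited form. The paired chi-square is a stated error: it cannot show a treatment effect and should be replaced, even though the article does not say which outcome it would be applied to. The unranked within-arm tests are a real risk to interpretation. With no treatment effect, a verdict of KDGs significant and placebo not would arise in about 11% to 25% of trials for common changes of 20 to 50, against 2.5% for a between-arm test. That range assumes SD 200 and 64 per arm, taken from the TPOAb calculation; 25% is the worst case, not a typical value, and the figure falls again when the common change is large.

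The analysis of the two scales is the weaker part. It is under-specified rather than shown to be wrong. The variance ratio of 0.65 to 0.85 depends on an assumed r and applies only if baseline is not already in the model. It measures baseline adjustment, so it should not be read as the loss from leaving out weeks 4 and 8, which would be modest for a week-12 contrast.

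The scales are secondary outcomes, TPOAb is measured only at baseline and week 12, and the sample size does not change. The revision is worth making but does not threaten the trial's design.

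**What to change.** 1. For any qualitative efficacy outcome, replace the paired chi-square with a between-arm chi-square test or logistic model at week 12, and name the outcomes to which it applies.
2. State that efficacy claims rest solely on the between-arm contrast. Report within-arm changes as estimates with 95% CIs and no P values.
3. Analyse the TCM and ThyPRO-39 scores with one between-arm mixed model for repeated measures on weeks 4, 8 and 12, with arm, visit, arm-by-visit, week-0 score and centre, and unstructured covariance. The week-12 contrast is the result. If the existing ANCOVA already includes the week-0 score, say so.

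The cost is revised wording, standard SAS procedures and a little more analysis work, with no new data. The Abstract says analysis has not been performed, while the Results section says it is in progress, so the change should be dated and its timing relative to unblinding recorded.
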